## Abstract

**Introduction:**

Alzheimer's disease is a neurodegenerative syndrome characterized by cognitive deficits, loss of daily functions, and mental and behavioral disorders, which cause stress and negatively affect the quality of life. Studies in the field suggest that combining cognitive training with physical activity can reduce the risk of developing the disease and, once neurodegeneration has begun, it slows its progress. In particular, virtual reality and augmented reality administer cognitive stimulation while providing a link to autobiographical memory through reminiscence, enabling the improvement of the person's quality of life. The present protocol aims to evaluate the effectiveness of cognitive and physical treatments, integrated with the addition of virtual reality and reminiscence elements, using the Brainer software, in which people will find cognitive training, and the jDome^®^ BikeAround™ system, which will allow participants to pedal along a personalized path projected on a schematic, using an exercise bike connected to the system.

**Methods and analysis:**

For this study, 78 patients with mild Alzheimer's dementia were recruited and divided into the Experimental Group (EG) and Control Group (CG). Sixteen treatment sessions of 60 min each were conducted for both groups (2 training sessions per week, for 8 weeks), including 1 patient at a time. The EG received cognitive treatment with Brainer and physical training with jDome, while the CG received cognitive treatment with Brainer and physical training with a classic bicycle. The evaluation mainly focused on the assessment of the person's cognitive status. Other analyses were conducted on the quality of life, mood, behavioral disorders, and physical function, which were considered secondary outcomes.

**Discussions:**

The ultimate goal of the present study is to test the effectiveness of a treatment for people with mild Alzheimer's focused on the integration of cognitive training and aerobic physical activity, using an exercise bike, with the addition of virtual reality and reminiscence elements.

**Ethics and dissemination:**

The study was approved by the Ethics Committee of the IRCCS INRCA. It was recorded in ClinicalTrials.gov on 2 June 2022 with the number NCT05402423. The study findings will be used for publication in peer-reviewed scientific journals and presentations in scientific meetings.

## Introduction

Dementia is a chronic neurodegenerative syndrome characterized by deficits in cognitive functions, associated with the loss of daily function and with mental and behavioral disorders. There are over one million people with dementia in Italy, of which 54% are due to Alzheimer's disease and about 16% are due to vascular dementia (1). Alzheimer's disease is a neurodegenerative disease with insidious onset and progressive impairment of behavioral and cognitive functions, including memory, comprehension, language, attention, reasoning, and judgment (2, 3). Neuropsychiatric symptoms, like apathy, social withdrawal, disinhibition, agitation, psychosis, and wandering, are sources of stress and negatively affect the quality of life of both the person with dementia and their caregiver (4).

There is no cure for Alzheimer's disease, although psychosocial interventions have been shown to be effective in improving the quality of life and psychological wellbeing of people with dementia (5–8); moreover, they are considered the treatment of choice for the management of psychological and behavioral disorders (9, 10).

Psychosocial interventions include a wide variety of strategies, ranging from emotional and behavioral approaches, physical training to cognitive stimulation, and psychological therapy (11). Psychosocial interventions aim to maximize the use of the remaining function, recruiting a compensatory network and preventing the disuse of brain function acting on the cognitive reserve, neural plasticity, and residual abilities of the person with dementia (12). Neural plasticity refers to the ability of the brain to change itself based on experiences that have been lived and learning throughout the life span. This ability is also maintained in Alzheimer's patients by determining modifications and the growth of some neuronal and synaptic pathways in the central nervous system, such as in the hippocampus and the entorhinal cortex. Stimulating neuroplasticity helps the person to compensate as much as possible for the damage produced by the disease. Moreover, also in the early/moderate stages of AD, cognitive reserve, which helps in the efficient use of strategies and functional connection networks between pre-existing neurons, compensates for neurodegeneration and allows the maintenance of patients' cognitive performance (13). Psychosocial interventions, therefore, do not alter disease progression in terms of structural neuropathology, but they act through functional brain changes and alter the structure of the association networks, like the default mode network connectivity (14, 15).

According to literature, cognitive interventions (16, 17), regular physical activity (9, 10), and reminiscence therapy appeared effective in the therapy of people with mild to moderate dementia (17).

Cognitive stimulation programs, computerized individual cognitive training, as well as physical exercise appear to be able to induce a significant improvement in cognitive performance, quality of life, and wellbeing in people with mild to moderate dementia (18–20).

Physical activity increases the availability of different classes of growth factors that stimulate hippocampal neurogenesis (21), neuronal plasticity (22), and the reduction of symptoms of depression (23). Several studies show, especially in the early stages of the disease, that stimulation and participation in various types of activities help to counterbalance the cognitive changes related to the pathology, thanks to cognitive plasticity (24, 25). Although in a recent review it emerged that the results of studies on the subject are inconsistent and of poor quality (26), other studies suggest that physical activity is able not only to delay the onset and reduce the risk of Alzheimer's disease but also to slow the functional decline after the onset of neurodegeneration (23, 27).

People with Alzheimer's disease who practice physical activity reported an improvement in daily function, a slowing of the decline in cognitive tests, a better physical performance associated with a reduced risk of falling, and a decrease in depressive symptoms compared to those who do not practice physical activity (23, 28). The WHO guidelines on reducing the risk of cognitive decline and dementia suggest that healthy elderly people perform at least 150 min of moderate-intensity aerobic physical activity per week (29). However, it has not yet been identified which type of systematic and structured physical activity is most effective in reducing the risk or slowing down cognitive decline in the elderly (30). There are currently no specific guidelines on what type of exercise (aerobic, strength training, balance training, or a combination of all of these), how often, and how long is most beneficial for specific forms, and the severity levels of dementia. (31). At the moment, multicomponent physical exercise is the most effective, bringing improvements in daily functionality and promoting autonomy (30). However, recent studies underline the need to take into account the risk of adverse events both physically (e.g., increased risk of falling, cardiovascular events during exercise) and the cognitive deterioration for people with dementia who adhere to aerobic exercise programs and of resistance, especially if of high intensity (31, 32).

Studies suggest that combining physical exercise with cognitive training may be a more successful strategy for promoting greater stability of cognition, improvement in apathy, mood, autonomy in daily living activities, and quality of life compared to physical exercise alone (33–35).

According to the literature, the exercise bike appears to be suitable for carrying out aerobic physical activity for people with dementia, and virtual cycling is an even more engaging and stimulating alternative to do it (36–38). This type of cycling makes it possible to recall the pedaling of youth and seems to encourage higher levels of physical activity (38). Furthermore, virtual reality and augmented reality offer the possibility of simultaneously providing cognitive stimulation and a connection to autobiographical memory through reminiscence, thus participating in the improvement of the quality of life of people with dementia (39). The World Health Organization stressed the importance to use technology to improve the treatment of dementia (40). Virtual experiences improve mood and reduce apathy and allow people with dementia to be simultaneously engaged in meaningful conversations, as well as in exercise activities (39, 41). In fact, virtual experiences are generally preferred by people with cognitive impairment over non-virtual experiences (39).

Karssemeijer et al. demonstrated that both interactively combined physical exercise with cognitive training in a virtual environment and standard aerobic training can induce an improvement in psychomotor speed, an important predictor of functional decline (33).

Finally, virtual reality can also be used to stimulate reminiscence and the recovery of more vivid memories in people with Alzheimer's (42). Reminiscence is a non-specific stimulation activity that consists of recalling in a structured way personal past events supported by memory triggers. The recall of memories from autobiographical memory (e.g., significant events in the person's life) becomes the tool to favor the recovery of emotionally pleasant experiences. Reminiscence therapy produces an improvement in the quality of life and mood of people with dementia (42–48).

Following this review of the literature and taking into account the limits already identified by the authors of the studies discussed above, we want to evaluate the effectiveness of an integrated cognitive and physical treatment with added virtual reality and reminiscence elements.

The training will be administered in an individualized way and will consist of two separate components carried out in sequence: first, a computerized cognitive training with the web platform “Brainer—Professional Brain trainer” (49) *via* tablet, and then a physical training motivated by reminiscence through the jDome^®^ BikeAround™ (in the text named jDome) system (50, 51), which connects a stationary bicycle to a monitor. The Brainer Professional web platform is a clinically proven medical device for the cognitive rehabilitation of people with mild-stage dementia (49).

The cognitive exercises on the Brainer platform aim to help participants use compensatory strategies and exploit their residual cognitive skills to improve or maintain daily functions. Therefore, the Brainer platform aim at modify the course of the disease, allowing participants to maintain their autonomy longer and to reduce the lack of interest, anxiety and depression that dementia entails.

The use of the jDome system, on the other hand, will allow participants to cycle through an individualized path projected digitally on a screen. The support of a psychologist will allow participants to recover memories and emotions associated with the places encountered along the way in a reminiscence activity. jDome offers the participant the opportunity to engage in a motivating reminiscence activity associated with physical activity, this association can have a positive impact on maintaining physical and cognitive abilities and reducing the risk of falling (50, 51). According to the literature, exposure to an environment rich in stimuli associated with the specific past life of each participant allows for an improvement in the autobiographical memory and the quality of life (44). It can be assumed that the possibility of virtually retracing the streets and places of one's youth also allows the person using jDome to achieve a similar result.

The jDome is a tool developed in Sweden that takes people with dementia on a virtual bicycle tour along the paths of memories (51). The jDOME device combines an exercise bike, a dome-shaped projector, and Google Street View technology. The destination is typed into the computer, and once the image is loaded it appears on the screen. Users sit on the bike and cycle to meaningful destinations (a childhood home, a vacation destination, the place where they got married) projected onto the screen in front of them. The set of pedals and bicycle handlebars placed in front of the screen allows people to move the image and control what they are seeing around them, as well as giving the person the feeling of actually setting the movement. Moreover, the type of activity proposed by the jDome system stimulates not only physical performance but also implicitly the visuospatial skills and spatial orientation of the subject. The system is an innovative program that encourages physical and cognitive training in a fun and interactive way (50). For the purposes of the study, an individualized path will be structured on the basis of the roads and places significant for each participant from which to recover life episodes and reactivate the emotions linked to them in the hic et nunc. Selecting the places where the person can virtually pedal allows to prepare an individualized multisensory multimedia environment to make the most of the potential of technology in the therapy of reminiscence (44).

There is currently a lack of studies on the effectiveness and usefulness of jDome system. One study reported a limited benefit in mental health and wellbeing for people with dementia who used the system in residential settings (52).

From the interviews, it is clear that the greatest benefits derived from using jDome fall within the emotional sphere because the mood improves by bringing to mind many good times past. Most people were happy after using jDome, while only a few had negative experiences of sadness and anxiety (52).

For the purpose of studying the effectiveness of a treatment based on the association of computerized cognitive training that uses the “Brainer” web platform *via* tablet to a virtual reality system for aerobic physical exercise (jDome), changes will be assessed in cognitive level, physical performance, and quality of life of people with mild Alzheimer's dementia.

## Methods and analysis

### Trial design

The study is designed as a single-blinded (outcome assessors) randomized controlled trial to test the effectiveness of a training program that combines the jDome virtual reality system for aerobic exercise with computerized cognitive training *via* tablet. The Experimental Group (EG) will receive computerized cognitive training with the Brainer web platform and aerobic training with the jDome system. The Control Group (CG), on the other hand, will receive computerized cognitive training with the Brainer web platform and aerobic training with a standard exercise bike.

Assessment will be performed at the baseline (T0), at the end of intervention (after 8 weeks-T1), and 3 months after the end of intervention (follow-up T2).

The primary aim is to assess the stabilization of the global cognition of people with mild-stage Alzheimer's disease at the Mini-Mental State Examination (MMSE) and at the Alzheimer's Disease Assessment Scale-Cognitive Subscale (ADAS-Cog).

The secondary aim is the analysis of the modification of the quality of life, mood, behavioral disturbances, and physical function in people with mild-stage Alzheimer's disease.

### Study setting

The study will be conducted at the Center for Cognitive Disorders and Dementia (CDCD) of the Neurology Unit of the Istituto Nazionale Ricovero e Cura per Anziani IRCCS INRCA, Ancona, Italy. The last version (second version) of the current protocol is dated 8 March 2022.

### Participants

The inclusion criteria are:

Aged 65 and over;Pre-existing diagnosis of Alzheimer's, in mild phase, according to the 2011 criteria of the National Institute on Aging-Alzheimer's Association (NIA-AA);Clinical Dementia Rating Scale CDR = 1;Mini-Mental State Examination MMSE > 19;Functional Ambulation Categories FAC ≥4;Tinetti scale ≥ 20;Presence of a contact family caregiverResiding at home.

The exclusion criteria are:

Failure to meet the inclusion criteriaSensory deficits not compensated by the use of prosthesesPsychological and behavioral disorders not compensated by drug treatmentMedical contraindication to moderate intensity aerobic exercise.

### Sample size

The sample size estimation for this study was carried out considering the changes in MMSE score and ADAS for the cases compared to controls as the main outcomes. In the study by Han et al. (53), 64 subjects with MCI or mild dementia were enrolled to take part in combined cognitive training, cognitive stimulation, reality orientation, physical therapy, reminiscence therapy, and music therapy. The scores of the MMSE and the ADAS significantly improved in the experimental group compared to the control group with the following effect sizes: 0.47 for MMSE and 0.35 for ADAS. Assuming the same effect sizes in a repeated measures ANOVA model (2 groups and 2 repeated assessments), setting the statistical power at 90% and a significance level equal to 0.05, the expected sample size should be 38 to capture an effect on the MMSE and 68 subjects for ADAS. Considering a 1:1 ratio between cases and controls and a potential dropout rate of 15%, the overall sample size should be 78 subjects (39 cases and 39 controls).

It is hypothesized that this sample dimension is more than sufficient to grasp a variation also for secondary outcomes for which a treatment effect size is assumed of a similar or higher entity than that identified for the primary outcome.

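### The sample sizes 38 and 68 reproduce as a group main effect averaged over two assessments, not as the comparison of change the trial targets, so the stated 90% power is not the power of that comparison

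*Protocol article*

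**What the plan says.** All of this is in the Sample size section of the protocol article. The target is change: "The sample size estimation for this study was carried out considering the changes in MMSE score and ADAS for the cases compared to controls". An earlier study of a combined intervention supplies the "following effect sizes: 0.47 for MMSE and 0.35 for ADAS". The model follows: "Assuming the same effect sizes in a repeated measures ANOVA model (2 groups and 2 repeated assessments"). Power is fixed at 90% with alpha 0.05. The result is that "the expected sample size should be 38 to capture an effect on the MMSE and 68 subjects for ADAS". ADAS, with the larger requirement, drives the final 78 after an allowance for dropout. The section then states that "this sample dimension is more than sufficient to grasp a variation also for secondary outcomes".

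The section does not say whether 0.47 and 0.35 are Cohen's f or standardised mean differences, which term of the ANOVA is tested, what correlation between assessments was used, or which two assessments are meant. Trial design lists three: baseline (T0), the end of the 8-week intervention (T1) and a follow-up three months later (T2). Recruitment places random allocation after the baseline evaluation.

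**The concern.** In a two-group, two-visit repeated-measures ANOVA, a treatment effect on change is the group-by-time interaction. The group main effect instead compares the arms on the average of the two visits. If the first visit precedes randomisation, its expected between-arm difference is zero, so averaging it with T1 halves whatever treatment has achieved. A sample size computed for the main effect assumes a gap of the same size at both visits, and randomisation rules that out at T0.

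What is at stake is how a null result is read. A non-significant ADAS-Cog comparison would be reported as coming from a trial with 90% power, although that figure was not computed for the comparison of change. The assurance about secondary outcomes leans on the same figure.

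**Working it through.** **Inputs from the Sample size section:** effect sizes 0.47 and 0.35; 2 groups; m = 2 assessments; power 90%; alpha 0.05; 1:1 allocation. **Assumption:** correlation ρ between the two assessments is not stated; 0.5 is used, with other values shown. All powers use the noncentral F distribution with 1 and N − 2 degrees of freedom (N − 3 when adjusting for baseline). Required N is the smallest even total reaching 90%.

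**Step 1: reproduce the plan's figures.** For the between-group main effect with the values entered as f, λ = f²·N·m / (1 + (m − 1)ρ).
- MMSE: 0.47² × 38 × 2 / 1.5 = 11.19, power 90.2% (N = 36 gives 88.6%).
- ADAS: 0.35² × 68 × 2 / 1.5 = 11.11, power 90.7% (N = 66 gives 89.9%).

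Both match exactly at ρ = 0.5. At ρ = 0.3 the pair would be 34/58, and at 0.7 it would be 44/76. With two equal groups the gap is 2f, so these f values mean gaps of 0.94 and 0.70 SD.

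**Step 2: the term that tests change.** For group by time with the same f, λ = f²·N·m / (1 − ρ). At ρ = 0.5 this needs 16 and 24. At ρ = 0, 0.3 and 0.7 it needs 26/46, 20/34 and 10/16. The requirement falls as ρ rises, so no non-negative correlation gives 38 and 68 here.

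**Step 3: power when the gap exists only at T1.** Take a gap of d SD at T1, zero at T0, and the plan's 68 completers. Both the main effect and the interaction then have f = d/4.
- Main effect: λ = (d/4)²·2N / (1 + ρ)
- Change (group by time): λ = (d/4)²·2N / (1 − ρ)
- Baseline-adjusted T1 difference: λ = (d²·N/4) / (1 − ρ²)

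For ADAS with d = 0.70, (d/4)²·2N = 0.030625 × 136 = 4.165 and d²·N/4 = 8.33. At ρ = 0.5 the three λ are 4.165/1.5 = 2.78, 4.165/0.5 = 8.33 and 8.33/0.75 = 11.11.

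| ρ | Main effect | Change | Baseline-adjusted T1 |
|---|---|---|---|
| 0.3 | 42% | 67% | 85% |
| 0.5 | 38% | 81% | 91% |
| 0.6 | 36% | 89% | 95% |
| 0.7 | 34% | 96% | 98% |

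At ρ = 0.5, 90% power for change at 0.70 SD needs 88 completers.

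**Step 4: the other reading of the metric.** If 0.35 is a standardised mean difference at T1, then at ρ = 0.5 with 68 completers λ for change is 0.0875² × 136 / 0.5 = 2.08, power 30%. The baseline-adjusted λ is (0.35² × 68/4) / 0.75 = 2.78, power 38% (66% at ρ = 0.8). For MMSE with 0.47 on this reading, the powers are 48% and 60%.

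**The case against.** The strongest reply is that N = 68 with about 90% power can be defended. A baseline-adjusted comparison at T1, with f defined at T1 and ρ = 0.5, has λ = f²·N/0.75, which equals the main-effect λ of f²·N·2/1.5. It therefore also returns 38 and 68. A group-by-time test with f defined at T1 returns them too if ρ = 0.625, since (f/2)²·2N/0.375 is again 1.333·f²·N. Both facts stand. A reader might infer that the figures can arise in only one way, or that 90% power can never apply to an effect appearing after baseline; neither inference is supported. What remains is that the section names a repeated-measures ANOVA, describes no baseline adjustment and states no correlation.

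A reader might also infer that the trial is certainly underpowered. The documents do not show that. For a 0.70 SD gap at T1, change-score power rises from 89% at ρ = 0.6 to 91% at ρ = 0.625. If 0.35 were the f of the interaction itself, power at ρ = 0.5 would exceed 99%, although that implies a T1 gap of 1.40 SD. The 30% and 38% figures depend on a metric that the text does not give and that cannot be settled without the cited study.

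Nor does the article say that the main effect will be the test. Data analysis names repeated-measures variance models without a term and defers to an analysis plan, so the 38% describes the term that was sized, not a declared analysis. Finally, if the two assessments were T1 and T2, the main effect would be a legitimate target. The section's reference to changes makes T0 and T1 the more natural reading.

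**Conclusion.** The point holds as a mismatch between the stated power and the comparison it is meant to support. Within the ANOVA that the section names, 38 and 68 are the between-group main effect with f = 0.47 and 0.35 and ρ = 0.5. With those same inputs they are not the group-by-time term. On the T0/T1 reading, the 90% is therefore not the power of the comparison of change.

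For ADAS-Cog, which drives N, the consequence ranges from none to serious. At a 0.70 SD gap at T1, a baseline-adjusted analysis keeps about 91% at ρ = 0.5 (85% at 0.3), and change gives 67% to 96% over ρ = 0.3 to 0.7. At 0.35 SD and ρ = 0.5, power is 30% to 38%. Which case applies depends on the metric, the tested term and the correlation, none of which is stated. The conclusion rests on ρ = 0.5 as the reproducing value and on T0 and T1 being the two assessments. The sentence on secondary outcomes has no calculation of its own and inherits the same uncertainty.

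**What to change.** Keep N and restate the Sample size paragraph:
- Say whether the cited 0.47 and 0.35 are Cohen's f or standardised mean differences.
- Name the two assessments, the tested term and the assumed correlation, with a short range for the correlation.
- Base the power statement on the baseline-adjusted arm difference at T1, and have the analysis plan name the same comparison. Suggested wording: *68 completers give about 90% power for a 0.70 SD difference in ADAS-Cog at T1, assuming a correlation of 0.5 with baseline, and about 38% power for a difference of 0.35 SD.*
- Requalify the sentence on secondary outcomes, either by giving the standardised difference that 68 completers can detect or by calling those analyses supportive without a power claim.

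The cost is one rewritten paragraph and no extra patients. The power statement becomes less favourable if the cited values prove to be standardised mean differences.

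### At the stated 15% dropout, 78 enrolled leave about 66 completers, not the 68 that the same paragraph requires for ADAS; the matching total is 80

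*Protocol article*

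**What the plan says.** The calculation is in the protocol article, Methods and analysis, Sample size. It takes effect sizes of "0.47 for MMSE and 0.35 for ADAS" from an earlier study, aims for 90% power at the 0.05 level, and assumes a "repeated measures ANOVA model (2 groups and 2 repeated assessments"). From these it concludes that "the expected sample size should be 38 to capture an effect on the MMSE and 68 subjects for ADAS". With equal allocation to the two arms and an allowance for dropout, it then arrives at its total: "a potential dropout rate of 15%, the overall sample size should be 78 subjects (39 cases and 39 controls").

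The figure 78 is repeated as the planned enrolment under Intervention and in the Methods and analysis paragraph of the Abstract. The article prints no inflation formula, no rounding rule and no other retention assumption.

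**The concern.** A dropout rate is a share of the people enrolled. An allowance for it should therefore give an enrolment which, after that share is lost, still leaves the required number. Here the required number, the dropout rate and the final total stand in one paragraph, and the total does not leave the required number.

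ADAS-Cog is one of the two named primary measures and sets the size of the trial, because its requirement of 68 exceeds the 38 for MMSE. What is at stake is whether the stated enrolment supports the stated 90% power at the stated dropout.

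**Working it through.** **Inputs, all from the Sample size section:** required N of 38 (MMSE) and 68 (ADAS); dropout 15%; allocation 1:1; total 78 (39 + 39); power 90%; alpha 0.05; effect sizes 0.47 and 0.35; two groups and two assessments.

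**Step 1. Reproduce the printed total.** Adding 15% to the required number gives 68 x (1 + 0.15) = 78.2, which rounds to 78.

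**Step 2. Apply the dropout to the enrolled number.**
- Completers from 78: 78 x (1 - 0.15) = 66.3, about 66 (33 per arm). Shortfall: 68 - 66 = 2.
- Enrolment needed for 68 completers: 68 / (1 - 0.15) = 80.0 (40 per arm). Check: 80 x 0.85 = 68.
- Largest dropout at which 78 still leaves 68: 1 - 68/78 = 12.8%.

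Because 80 is an exact, even whole number, neither rounding nor equal allocation explains 78. This step uses only printed figures.

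**Step 3. What the shortfall does to power.** This step needs assumptions that the article does not state: the effect sizes are Cohen's f, the test is the between-groups effect, and the correlation between the two assessments is rho = 0.5. With m = 2 assessments, the F test has 1 and N - 2 degrees of freedom and noncentrality

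lambda = f² x N x m / (1 + (m - 1) x rho) = f² x N x 2 / 1.5.

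The smallest even N reaching 90% power is 38 for f = 0.47 and 68 for f = 0.35. Both match the printed values, so the assumptions are plausible.

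ADAS (f = 0.35) in the same model:

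| Completers | lambda | Power |
|---|---|---|
| 66 | 0.1225 x 66 x 2 / 1.5 = 10.78 | 89.9% |
| 67 | 0.1225 x 67 x 2 / 1.5 = 10.94 | 90.3% |
| 68 | 0.1225 x 68 x 2 / 1.5 = 11.11 | 90.7% |

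MMSE power (f = 0.47) at 66 completers is 99.1%.

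**Step 4. Sensitivity to the unstated correlation.** At 66 completers, ADAS power is 91.7% if rho = 0.4 and 87.9% if rho = 0.6. At rho = 0.6, even 68 completers give only 88.9%.

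**The case against.** The strongest reply is that the slip makes no practical difference. In the reconstructed model, power reaches 90% at N = 66.3, and 68 is simply the next even whole number. The expected 66.3 completers therefore sit almost exactly on the target, and 66 whole patients fall about 0.1 percentage point below it. The unstated correlation moves power far more than two patients do. All of this stands, and it limits the weight of the point. It does not make 68, 15% and 78 compatible.

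It may also be said that adding 15% to the required number is a common convention. But the text calls the figure a dropout rate, and on the plain meaning of that term the total falls short.

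Two stronger readings are tempting, and the document supports neither. A reader might infer that the trial is materially underpowered for ADAS; the calculation shows a difference of less than one percentage point (90.7% to 89.9%), and that rests on assumptions the article does not print. A reader might also take it as established that the authors multiplied by 1.15. The match with 78.2 makes this likely, but no formula is given. The inconsistency does not depend on it, since 78 x 0.85 is below 68 however 78 was reached.

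**Conclusion.** The point holds as a minor arithmetic correction. On the printed figures alone, 78 enrolled at 15% dropout is two completers short of the ADAS requirement; 80 is the total that meets it, and 78 tolerates 12.8%. Nothing else in the article resolves the conflict.

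The consequence is very small: about 0.8 percentage points of ADAS power (90.7% - 89.9%), conditional on Cohen's f = 0.35, a between-groups test and rho = 0.5. The MMSE requirement is unaffected. The point gives no reason to change the design or the analysis.

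**What to change.** Either of two changes makes the paragraph consistent.

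1. **Keep 78 and restate what it delivers.** Say that 78 retains the required 68 only if dropout is at most 12.8%, and that at 15% dropout about 66 complete, giving ADAS power just under 90% (about 89.9%, with the assumptions stated). Giving 66 completers without the power statement would not be enough, because the paragraph would still require 68. The 12.8% should be presented as the limit that 78 can absorb, not as a new dropout forecast, unless there is evidence for it. Cost: a sentence or two in the Sample size section, and no new patients.

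2. **Correct the total to 80 (40 + 40).** Change the total and the split in the Sample size section, and the repeated 78 under Intervention and in the Abstract. Cost: edits in three places and two more patients.
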